## Abstract

**Background:**

Acute pain is always the most common complaint in Emergency Department admissions and options for analgesia are limited. Nitrous oxide/oxygen possess many properties showing it may be an ideal analgesic method for the Emergency Department; it is quick-acting, well-tolerated, and does not mask signs and symptoms. The aim of this study is to evaluate the safety and analgesic effect of the fixed nitrous oxide/oxygen mixture for trauma patients in a busy emergency environment.

**Methods:**

The randomized, double-blind, prospective, placebo-controlled study will be carried out in the Emergency Department of General Hospital of Ningxia Medical University. The target research objects are trauma patients who present to the Emergency Department and report moderate to severe intensities of acute pain. A total of 90 patients will be recruited and randomly assigned into the treatment and control group. The treatment group will receive conventional pain treatment plus nitrous oxide/oxygen mixture and the control group will receive conventional pain treatment plus oxygen. Neither patients, nor investigators, nor data collectors will know the nature of the gas mixture in each cylinder and the randomization list. Outcomes will be monitored at baseline(T0), 5 min (T1), and 15 min (T2) after the beginning of intervention and at 5 min post intervention (T3) for each group. The primary outcome is the level of pain relief after the initial administering of the intervention at T1, T2, and T3. Secondary outcomes include adverse events, physiological parameters, total time of the gas administration, satisfaction from both patients and healthcare professionals, and the acceptance of patients.

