### Outcome measures

#### Primary outcome measure

The primary outcome measure will be the level of pain relief after the initiation of the intervention, which is assessed and recorded by the data collector according to the pain level provided by patients using a self-assessment scale (NRS).

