### Sample size determination

Based on our previous studies on cancer breakthrough pain and burn-dressing pain [32, 34], this study uses pain severity as the primary endpoint measure for sample size calculation. We used preliminary visits obtained in our ED for 20 patients and calculated the sample size at 5 min (T1) and 15 min (T2) after the beginning of intervention. It is observed that 65% of patients receiving premixed nitrous oxide/oxygen had pain relief at T1 compared with 8% of patients receiving oxygen (a decrease in pain intensity of at least 30% was recommended as the pain relief [35]). We found that 70% of patients in the experimental group experienced pain relief at T2 versus 10% in the control group. It aimed to determine a appropriate target sample size that would provide a 90% power (*β* = 0.10) for two-tailed testing with 5% type-1 error rate of the measure. We separately calculated a minimum requirement of 30 patients or 24 patients for total with the formula [36, 37]. In practice, we finally decided on 90 samples (45 per group) to improve the power of this study.

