### Data analysis

SPSS version 22.0 (Chicago, IL, USA) will be used to conduct the statistic analysis, initially according to the intention-to-treat principle. All patients randomized should be included in the analysis and missing data will be handled using multiple imputation. Descriptive statistics will be adopted to describe the population demographic data by medians (interquartile ranges [IQR]; min–max), means (standard deviations), and proportions (exact binomial 95% confidence intervals [CIs]), as appropriate. The comparison of means will be assessed by Student’s *t* test or non-parametric test and using the Mann–Whitney test to compare means of continuous variables if applicable. Chi-squared tests or Fisher’s exact test will be performed to compare the proportions of categorical variables. The analysis of physiological parameters and scores at baseline, T2, and T3 were performed by analysis of covariant (ANCOVA) adjusting for the respective baseline value on the two groups (“experimental” and “control”). We considered all *P* values < 0.05 to be statistically significant.

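### The primary outcome has no settled time point and no rule for combining T1, T2 and T3, so if any one P < 0.05 counts as success, the false-positive rate can exceed the planned 5%

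*Protocol article*

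**What the plan says.** Four places in the protocol article bear on this.

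- **Abstract, Methods:** "The primary outcome is the level of pain relief after the initial administering of the intervention at T1, T2, and T3". That is three time points: 5 and 15 minutes after the start of inhalation, and 5 minutes after it ends.
- **Primary outcome measure:** "The primary outcome measure will be the level of pain relief after the initiation of the intervention". The instrument is the NRS, and no time point is named.
- **Sample size determination:** the design is for "two-tailed testing with 5% type-1 error rate of the measure" with 90% power. Relief is defined as a fall in pain intensity of at least 30%. Two sets of rates are used: "65% of patients receiving premixed nitrous oxide/oxygen had pain relief at T1 compared with 8% of patients receiving oxygen", and "70% of patients in the experimental group experienced pain relief at T2 versus 10% in the control group". The result is "We separately calculated a minimum requirement of 30 patients or 24 patients for total with the formula". The planned total is then raised to 90, 45 per group. T3 is not used.
- **Data analysis:** "We considered all *P* values < 0.05 to be statistically significant". Proportions are to be compared by chi-squared or Fisher's exact test. Scores are analysed by ANCOVA adjusted for baseline, in a sentence that lists baseline, T2 and T3 but not T1.

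**The concern.** The three places that could fix the primary time point give three different answers: T1, T2 and T3; none; and T1 and T2. The only stated significance rule is an unadjusted 0.05 applied to every P value. If the time points disagree, a reader cannot tell from the protocol whether the primary outcome was met. The investigators could claim whichever time point came out significant, and could choose it after unblinding.

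This is more than detail left to an analysis plan. The article does state a significance rule, and the choice of primary time point belongs in the protocol. The result also carries weight: the Abstract and Discussion say that success could feed into preliminary guidelines, and the Abstract adds wide implementation in Emergency Departments.

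**Working it through.** **Inputs from the protocol.** Two-sided α = 0.05; power 0.90; responder rates 65% vs 8% (T1) and 70% vs 10% (T2); minimum totals 30 and 24; planned 45 per group; three primary time points (Abstract) or two (sample size).

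**Input not in the protocol.** The correlation ρ between the test statistics at different time points. It is assumed and varied below.

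**1. The plan's own sample sizes.** With z = 1.960 and 1.282, p̄ the mean of the two rates and d their difference:

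- Simple pooled formula, n per group = 2p̄(1−p̄)(1.960+1.282)²/d². At T1, p̄ = 0.365 and d = 0.57, so n = 14.99, rounded up to 15, total 30. This matches.
- Fleiss formula without continuity correction, n = [1.960√(2p̄(1−p̄)) + 1.282√(p₁(1−p₁)+p₂(1−p₂))]²/d². At T2, p̄ = 0.40 and d = 0.60, so n = 11.79, rounded up to 12, total 24. This matches.

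No single two-sided formula tried gives both totals (Fleiss gives 26 at T1, pooled gives 30 at T2), but each follows from a standard variant. Each is a calculation for one comparison at α = 0.05, with no allowance for a second or third.

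**2. Score comparisons, any time point below 0.05.** With independent tests the rate is 1 − 0.95³ = 14.3% for three and 1 − 0.95² = 9.75% for two. With a common correlation ρ it is P(any |Z| > 1.96) under a multivariate normal:

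| ρ (assumed) | any of three | T1 or T2 only |
|---|---|---|
| 0 | 14.3% | 9.75% |
| 0.5 | 12.5% | 9.1% |
| 0.7 | 10.9% | 8.4% |
| 0.8 | 9.8% | 7.8% |
| 0.9 | 8.4% | 7.0% |

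At ρ = 0.95 the three-point figure is 7.4%. Counting only false claims in favour of the gas, the three-point figure is about 4.2% (ρ = 0.9) to 7.3% (ρ = 0), against a nominal 2.5%.

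**3. Responder comparisons.** Binary outcomes were simulated under no difference, 45 per group, three time points, with assumed latent correlation from 0 to 0.9 and assumed common responder rates from 9% to 50%:

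- uncorrected chi-squared: about 10–17% for any of three;
- Fisher's exact: about 4–9% for any of three. At a responder rate near 10% it is about 5–6%, because a single Fisher test there has an actual error of only about 2%.

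**4. Rules that hold the error at 5%.** Bonferroni uses 0.05/3 = 0.0167 per time point. A fixed sequence (T2 tested only after T1 succeeds), a single named time point, or a requirement that all succeed also holds it at or below 5%.

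**5. Power after the repair.** At 45 per group, exact power for 65% vs 8% and for 70% vs 10% exceeds 99.9% at α = 0.05. It still exceeds 99.9% at α = 0.0167, with either chi-squared or Fisher's test.

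**The case against.** The strongest reply is that the protocol never says one significant time point is enough. Data analysis sets a threshold for calling a P value significant; it does not define a positive trial. If one time point decided, or all had to succeed, the error would be at or below 5%. It can also be said that the 5% in the sample size section is a per-comparison rate, since the two calculations were done separately, and that no familywise 5% was promised.

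Both points stand as limits on the claim. A reader might infer that the trial has adopted an any-one-suffices rule, or that its type I error simply is 8–14%. The text supports neither. It leaves the rule open while calling every P < 0.05 significant, so the inflated rates apply only under the permissive reading.

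Three further limits stand. The count of three time points rests on the Abstract alone. The 14% end needs independence, which is implausible for NRS ratings taken minutes apart in the same patient. The test matters too: with Fisher's exact test there may be almost no inflation, and with uncorrected chi-squared it can exceed the range for scores.

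The reply that multiplicity may be handled in an analysis plan not shown carries less weight. It would not remove the disagreement over the primary time point within this document, or the general significance rule it states.

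**Conclusion.** The point holds in conditional form. The protocol is inconsistent about its primary time points and gives no rule for combining them. If a significant result at any one of them is taken as a positive primary result, the two-sided false-positive rate generally exceeds the planned 5%. It is about 8–14% for three score comparisons at correlations of 0.9 to 0, about 7–10% for T1 and T2 only, about 10–17% for three responder comparisons by uncorrected chi-squared, and about 4–9% by Fisher's exact test, where the excess may vanish. These ranges rest on assumed correlations and, for responders, assumed common response rates; the protocol gives no correlations.

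A reader might also infer that the sample size is too small once multiplicity is handled. It is not: at the protocol's own rates, 45 per group leaves power above 99.9% after adjustment. The defect is in the definition of success, and it is cheap to repair.

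**What to change.** Before unblinding, amend the protocol to:

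1. Name one primary time point, one measure and one test, for example the proportion with at least 30% pain reduction at T1. T1 is natural because it gave the larger of the two minimum totals.
2. Test T2 only if T1 is significant at two-sided 0.05, and make T3 secondary. Bonferroni at 0.05/3 across all three is an equally valid alternative if the investigators want each time point to be able to carry the claim.
3. State that only this procedure supports the primary conclusion, and limit the general P < 0.05 sentence accordingly.
4. Align the Abstract, Primary outcome measure, Sample size determination and Data analysis sections, and add T1 to the ANCOVA sentence.

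**Cost.** Recruitment began in November 2017, so this is an amendment during recruitment. The Ethics and dissemination section requires changes to outcomes to be communicated to the DMC, clinicians, participants and the ethics committee. Under the fixed sequence, a lone positive at a later time point can no longer be claimed as primary success. No additional patients are needed.

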**Discussion:**

Our previous studies suggested that a fixed nitrous oxide/oxygen mixture was an efficacious analgesic for the management of burning dressing pain and breakthrough cancer pain. The results of this study will provide a more in-depth understanding of the effect of this gas. If this treatment proves successful, it could help to generate preliminary guidelines and be implemented widely in trauma patients with pain in Emergency Departments.

**Trial registration:**

Chinese Clinical Trial Register, ChiCTR-INR-16007807. Registered on 21 January 2016.

**Electronic supplementary material:**

The online version of this article (10.1186/s13063-018-2899-6) contains supplementary material, which is available to authorized users.

## Background

Despite there are extensive research on the etiology of pain, barriers to pain management, advanced analgesia approach, and evidence-based guidelines for the pain management such as the World Health Organization three-step analgesic ladder, acute pain remains a common complaint observed in the Emergency Department (ED) with a high prevalence of up to 90% [1–3]. Over the past decades, emergency health workers have documented that the prevalence of pain undertreatment is high. Numerous studies demonstrated that 60–80% of patients reported pain on admission to the ED [2, 4, 5]. It continues to be a challenge for emergency healthcare givers to treat oligoanalgesia or undertreatment of pain [6]. A prospective cross-sectional study assessed 525 ED patients’ experiences and satisfaction with pain management and reported that only half of patients received analgesics even though 63% suffered with severe pain. The average time to analgesic administration was almost 2 h and the percentage of patients who received analgesics within 1 h after arrival was only 29% [7]. In a retrospective medical record study, Wilson and Pendelton [8] found that no more than half of patients admitted to the ED for acute pain were treated with analgesics during hospitalization. Of these, nearly 70% of patient waited > 1 h and > 40% waited > 2 h for analgesics. In another prospective study conducted in the ED of a teaching hospital in Central Africa, nearly 50% of the patients did not receive prescribed analgesia before definitive surgical treatment, including most patients with severe pain [9]. These observed results are consistent with previous studies [10, 11]. Taking into account previous reports, the results of these studies show that the practice of oligoanalgesia in the ED is a global phenomenon, partially because emergency health workers fail to fully assess or perceive the patient’s pain intensity [9]. All in all, the percentage of patients who receive any type of analgesia and pain relief is still deficient.

Efforts to treat acute pain are priorities for ED healthcare to consider. Patients expect analgesia rapidly in the ED, which is not met in many ED [12]. Several reasons have been related to poorly managed pain. First, the failure assessment or lack of skills to assess patients’ pain is a main predicting factor of pain treatment deficiency. The physicians’ underestimation of pain can be circumvented by using the pain assessment scales [13–15]. Second, in our institution, no analgesic guideline exists to help the physician prescribe analgesics for patients in need and no effort was made to influence physicians’ orders for analgesia [4]. Physicians are also worried about concealing, delaying, or obscuring diagnosis [11, 16], although there is poor evidence of this. There are still many myths and misconceptions about opioids, addiction, and tolerance [17, 18]. We likewise have a limited ability to monitor the cardiopulmonary function of opiates in the ED. Third, a crowded ED setting and insufficient ED staff affect acute pain assessment and reassessment [19]. It is probable that busy healthcare professionals pay less attention to complaints of painful conditions. In fact, pain management is not a priority in assessing and resuscitating these patients traditionally. Other factors including gender, race, age, education, language, and cultural and socioeconomic backgrounds also play important roles in the disparity of treatment [20–23].

However, patients with unrelieved pain lead to a stress response consisting of increased heart rate and blood pressure, impaired immune function, systemic vascular resistance, and altered release of neuroendocrine, pituitary, and other hormones [24]. These responses could limit patients’ recovery from injury, resulting in longer hospitalization, higher readmission rates, and more frequent outpatient visits. These factors may lead to lower rates of ED patient satisfaction and an increase in medical cost [25]. Hence, acute pain management should be a priority for us to consider and we have several reasons to search for safe and universal analgesics.

Nitrous oxide/oxygen is a self-administered inhaled gas reserved in a pre-prepared cylinder. Its analgesic effect has been known for nearly two centuries [26]. It has few side effects, all of which disappear after termination of exposure to the gas. There is no need for an endovenous procedure. The patients’ self-sustained facemasks lower the risk of overdose as the patients’ level of consciousness control their ability to maintain the gas flow [27]. Therefore, it is safe and non-invasive [28]. Owing to its low solubility in blood and not bound to proteins, it possesses the properties of rapid onset (no more than 2 min) and is quickly reversible after discontinuation (< 1 min). As a result, nitrous oxide does not obscure the signs and symptoms that may be necessary for subsequent damage or disease definitive diagnosis. It is reported that the mixture will play the same role as of a 15-mg dose of morphine given intramuscularly [29]. These properties also suggest that nitrous oxide/oxygen may be an ideal analgesic for ED use. Taking these advantages into account, we hypothesize that a fixed concentration of nitrous oxide/oxygen mixture (Patent no. ZL 2013 1 0053336.X) can provide superior analgesic effects for trauma patients with acute pain in the ED.

## Methods/design

### Aim

The primary aim of the current study is to determine the clinical analgesic effect of the fixed nitrous oxide/oxygen mixture on trauma patients with acute pain when compared with the control group. It is measured by pain relief level. Secondary objectives of this trial include:Evaluating the clinical use safety of the fixed gas by physiological parameters and adverse effects.Assessing the satisfaction of both patients and healthcare workers with pain treatment.Investigating patients’ acceptance for the new analgesia method.

### Study design

This is a single-center, prospective, randomized, double-blind, placebo-controlled, two-arm, superiority study. It was designed to test the analgesic effect and safety of inhaling premixed nitrous oxide/oxygen use in adult trauma patients with moderate to severe acute pain. This protocol was drafted using the SPIRIT guidelines [30] (see Additional file 1) and following the checklist of the Consolidated Standards of Reporting Trials (CONSORT) statement (see Additional file 2). The clinical trial was reviewed and approved by the Ningxia Medical University Ethics Committee. This study has been registered at Chinese Clinical Trial Registry (registration no. ChiCTR-INR-16007807). The whole study design is provided in Fig. 1. Additionally, a SPIRIT figure for the schedule of enrolment, interventions, and assessments is presented in Fig. 2.

**Fig. 1 Fig1:**
[figure not shown]
Study design. NRS numerical pain rating scale, BP blood pressure, HR heart rate, SpO_2_ oxygen saturation, CTO conventional pain treatment plus oxygen, CTN conventional pain treatment plus nitrous oxide/oxygen mixture

**Fig. 2 Fig2:**
[figure not shown]
SPIRIT *figure*: schedule of enrolment, interventions, and assessments

### Study setting

This study will be carried out in the ED of General Hospital of Ningxia Medical University. This institution is an urban, public, 4500-bed, tertiary-care teaching hospital located in Northwest China, with an ED census of 179,117 annually.

### Study participants

All trauma patients who present to the ED will be invited to participate. The specific inclusion criteria are: patients who speak Chinese; aged ≥ 18 years; report moderate to severe intensity of acute pain upon admission (defined as a pain score ≥ 4 according to the Numerical Rating Scale [NRS]); are able to take deep breaths to use the self-managed device; are willing to participate in the study and sign informed consent. Patients are ineligible if they have considered contraindications to using the premixed gas (intracranial hypertension, recent ophthalmic surgery, epilepsy, unconsciousness, pneumothorax / hemothorax, facial traumas, intestinal obstruction, pulmonary embolism, emphysema, sinusitis, and retinal detachment [17]). Other exclusion criteria are: recent receipt of analgesics within 6 h; life-threatening situations or instability of clinical vital signs; pregnancy; individuals in police custody; or individuals included in another study.

All participating clinicians will be associate chief physicians, will have worked in the ED for > 5 years, and will be willing to participate in and receive training from the originator who conceived and designed the protocol. In this trial, two fixed clinicians who meet all the above criteria will be included.

### Interventions

All patients entering the ED will receive regular assessments by the clinician. The patients who meet all pre-specified inclusion and exclusion criteria will be introduced to the study. Investigators will explain the purpose, benefits, and potential risks of the study in detail to the patients. If the patients agree to participate in this study, they will be asked to sign an informed consent form and then be recruited. Subsequently, the relevant treatment will be carried out immediately. During the implementation of the intervention, the patients are randomly allocated to inhale either a fixed concentration of premixed nitrous oxide/oxygen or oxygen through a specially designed facemask with a one-way valve. The treatment group will receive nitrous oxide/oxygen mixture in addition to conventional pain treatment and the control group will receive oxygen in addition to conventional pain treatment. In this study, the oxygen cylinder is designed exactly the same as the nitrous oxide cylinder and oxygen is safe and readily available in the selected ED. We chose oxygen plus conventional pain treatment as a comparator to ensure the full consistency between treatment group and control group and the double-blind design. Gas inhalation will be administered continuously up to a maximum inhalation time of 15 min. Practitioners will be permitted to use other pain management forms in accordance with patients’ pain intensity after finishing the intervention. The trained investigator will successively include participants until they reach the target sample size and the project manager will assign participants to interventions according to the randomization list.

Generally, both nitrous oxide/oxygen and oxygen are considered safe interventions with no severe side effects for the participants. If side effects occur (e.g. dizziness, nausea) during the implementation of nitrous oxide/oxygen, they are usually short-lived and mild [28]. If any undesirable events occur or the participant requests to cease the intervention they received, the investigator can discern whether the trial will be continued. In all cases, the reason for discontinuation will be documented by the data collector.

There are many strategies to improve the adherence of the intervention. Before the start of the intervention, investigators will detail the duration of the intervention, the method of using the device, possible adverse effects, and give psychological support to participants. During the treatment, the patients’ physiological parameters are monitored and patients are asked if they feel uncomfortable or not. If they are uncomfortable, this is address immediately to ensure the ongoing safety of patients is accomplished. Adherence of intervention protocols will be ascertained by accomplishment of the intervention. We planned to develop a Supervision Adherence Form (SAF) for this trial to enable collation of patients’ adherence to facilitate reporting.

